### ***Quantitative methods***

In Stage 1 and 2, for the quantitative aspect, we anticipate recruiting 600 participants which will provide 80% power to detect an odds ratio of 2 for uptake of STI testing assuming a prevalence of the variable of interest in the control (non-STI testing) group of 30%. This assumes an uptake of STI testing of one third, giving 200 cases and 400 controls. Descriptive statistics will show the socio-demographic characteristics and distribution of knowledge, attitudes, and practices regarding STIs. Categorical variables will be described using

frequencies and percentages. Continuous variables will be described using either mean (standard deviation) or median (interquartile range) for normally distributed and non-normally distributed data, respectively. Logistic regression will be performed to determine factors predicting acceptance of STI testing.

For the prevalence survey, we anticipate recruiting 300 participants per cluster in the two provinces that will offer STI testing for at least 12 months before the endline survey is conducted (Harare and Bulawayo). Urine samples will be collected on randomly allocated days that the survey will be implemented. The days on which urine samples will be collected will be selected by block randomisation with 55% of survey days selected to allow for refusals etc.

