### ***u. 7.3 Statistical analysis***

CONSORT guidelines for cluster randomised trials will be followed. A flowchart will be created showing the number of clusters eligible, the number allocated to each arm and the number of participants per cluster in the cross-sectional survey. Cluster-level analyses will be used to adjust for between-cluster variability, as recommended for trials with fewer than 15 clusters/arm. Descriptive analysis will be used to compare the cluster-level characteristics of the two arms, with adjustment for variables that are imbalanced between arms (avoiding variables likely to be affected by the intervention) and for stratum.

All outcomes are binary. For each outcome, the risk for each cluster will be calculated, and shown by strata and arm. The mean and SD of the log risk will be used to estimate the geometric mean and associated 95%CI for each arm of the study. Linear regression of the log mean risk on strata and arm will be used to estimate the risk ratio and 95%CI. The approximate variance for the mean risks will be obtained based on the residual mean square from a 2-way ANOVA on arm and strata. A 95% CI for this will be calculated from the variance using a t-statistic.

Pre-defined sensitivity analysis will include multiple imputation to adjust for non-participation in the survey. Participants in the intervention clusters are not necessarily expected to have received the intervention personally. As a form of exploratory analysis we will assess the difference in outcomes between intervention arm participants who accessed the CHIEDZA intervention (defined as having had at least one HIV test through the CHIEDZA service), compared to control arm participants.

- **8. Ethical Considerations**

- **8.1 Collaborative partnerships**

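### The 80% power given for the STI-testing uptake sub-study does not follow from its printed inputs, which give about 97% for an odds ratio of 2 (two-sided 5% level assumed)

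*Combined protocol and SAP*

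**What the plan says.** The calculation is in protocol section 5.5.3, under Quantitative methods, and covers stages 1 and 2 together. The plan expects to recruit "600 participants which will provide 80% power to detect an odds ratio of 2 for uptake of STI testing". The factor under study is taken to be present in 30% of the clients who were not tested, who serve as the controls. The group sizes rest on one further assumption: "This assumes an uptake of STI testing of one third, giving 200 cases and 400 controls". The planned analysis is given in one line: "Logistic regression will be performed to determine factors predicting acceptance of STI testing".

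The text gives no significance level, sidedness, design effect, multiplicity allowance, covariate adjustment or non-response allowance for this calculation. The nearest indication of a level is in section 7.3, for the main cluster-level analysis: "Linear regression of the log mean risk on strata and arm will be used to estimate the risk ratio and 95%CI". That concerns a different analysis and is only indirect support for 5% two-sided.

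**The concern.** Every input except the significance level is printed, so the stated power should be reproducible to within a point or two. It is not: the conventional calculation gives a figure about 17 percentage points higher.

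This is the only numerical justification for the 600 participants, and it supports objective 5 in section 5.5.2 (factors predicting acceptance of testing). As printed, a reader cannot tell what the sample was sized for: an odds ratio of 2 with an allowance that was left out, a smaller odds ratio, or a factor with a different prevalence. These possibilities have different consequences. An allowance for clustering by service site, for instance, would call for a matching term in the analysis, and the one-line logistic regression plan has none.

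**Working it through.** **Inputs (section 5.5.3)**
- Testers n1 = 200; non-testers n0 = 400
- Prevalence of the factor among non-testers p0 = 0.30
- Odds ratio = 2
- Stated power = 80%
- Assumed, because not printed: two-sided 5% level (z = 1.96) and independent participants

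**Step 1. Prevalence among testers.** Odds among non-testers = 0.30/0.70 = 0.4286. Doubled, 0.8571. So p1 = 0.8571/1.8571 = 0.4615, and the difference is 0.1615.

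**Step 2. Attempt to reproduce the 80%.** Two-proportion test, with pooled variance under the null and unpooled under the alternative:
- Pooled proportion = (200 × 0.4615 + 400 × 0.30)/600 = 0.3538
- Null standard error = √[0.3538 × 0.6462 × (1/200 + 1/400)] = 0.0414
- Alternative standard error = √[0.4615 × 0.5385/200 + 0.30 × 0.70/400] = 0.0420
- Power = Φ[(0.1615 − 1.96 × 0.0414)/0.0420] = Φ(1.91) = **97.2%**

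The 80% is not reproduced. Other standard methods agree: 96.6% with continuity correction, 97.2% with a Wald test of the log odds ratio (the closest match to simple logistic regression), and about 97% with Fisher's exact test by simulation.

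**Step 3. What 80% power corresponds to.**
- Same 200 and 400, p0 = 0.30: odds ratio about 1.66 (79.2% at 1.65, 83.7% at 1.70).
- Odds ratio 2, p0 = 0.30, 1:2 split: 105 + 210 = 315 participants (80.3%), or 342 with continuity correction.

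**Step 4. Other readings of the printed inputs.**

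| Reading | Power |
|---|---|
| One-sided 5% | 98.7% |
| Two-sided 1% | 90.4% |
| Two-sided 0.1% | 72.6% |
| Protective factor, odds ratio 0.5 | 91.8% (Wald 89.6%) |
| 30% as overall prevalence | 96.1% |
| 30% as uptake in the unexposed; 50%, 30%, 20% exposed | 98.4%, 96.5%, 91.1% |
| Equal split, 300 and 300 | 98.4% |

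The equal split matters because Recruitment in section 5.5.3 selects equal numbers of accepters and decliners in stage 1. A more balanced split raises power, so it cannot explain the lower figure. The uptake reading crosses 80% only at an exposed share between 15% (84.3%) and 10% (71.1%). The plan prints no such share, and this reading changes what it says the 30% is.

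**Step 5. Unprinted assumptions that would give about 80%.**

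| Assumption | Power |
|---|---|
| Design effect 1.9 | 80.4% |
| Bonferroni allowance for 20 factors | 80.6% |
| Half the sample (100 and 200) | 78.4% |
| Prevalence among non-testers 10% | 79.1% |
| Prevalence among non-testers about 80% | about 80% |

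The design effect agrees with step 3: 600/315 = 1.90.

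**The case against.** The strongest reply is that the 97% is itself conditional. The plan prints no significance level, and participants come from several service sites and will be examined for many possible predictors. A design effect near 1.9, a correction for about 20 factors, or variance inflation from covariate adjustment (an R-squared of about 0.47 gives 80.7%) would bring the power to about 80% with every printed input unchanged. This stands to the extent that one cannot say the power or a printed input must be wrong; an allowance may have been used and left out. It does not rescue the text, which mentions no allowance.

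A second reply is that nothing is at risk, because 600 is more than enough for the stated contrast. That is correct on direction, and it limits the weight of the point. It does not make the stated power right.

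A reader might also infer that the sub-study is nearly twice as large as it needs to be. The documents do not support that. The 315 applies to one factor at 30% prevalence. The same 600 serve the search for other factors, some probably rarer, and the description of knowledge, attitudes and practices (sections 5.5.2 and 5.5.3).

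**Conclusion.** The stated power does not follow from the stated inputs. Assuming a two-sided 5% level and no design effect, it is about 97% rather than 80% for an odds ratio of 2, and 80% power corresponds to an odds ratio of about 1.66. This is an error of statement, or an undisclosed assumption, in a single sentence. It is conservative: on the printed inputs, power for an odds ratio of 2 exceeds 80%. The main trial outcomes and the separate STI prevalence calculation (Table 8) are unaffected.

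Because about 10% prevalence gives nearly 80%, a reader might infer that the 30% is a slip for 10%. That value comes only from solving backwards. A prevalence of about 80%, an odds ratio of about 1.66, or a design effect of about 1.9 fits equally well, and nothing in the documents singles one out.

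**What to change.** Replace the power sentence in section 5.5.3 with one that states the level and agrees with the inputs. For example: 600 participants (200 testers, 400 non-testers) give about 97% power for an odds ratio of 2, or 80% power for an odds ratio of about 1.66, at 30% prevalence among non-testers and a two-sided 5% level.

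If the 80% rests on a design effect, a multiplicity allowance or a different input, print that value and its source instead. If clustering by service site was allowed for, also account for site in the logistic model. The printed prevalence should not be altered to a back-solved value; only the original calculation can show whether another figure was used.

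The cost is one sentence, plus a site term in the analysis plan if clustering was the reason. The recruitment target need not change.

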#### **iv.5.5.4 Outcomes**

Outcomes will be:

1. Qualitative summary of knowledge, attitudes and practices regarding STIs
2. Qualitative summary of attitudes and practices regarding STI testing
3. Qualitative summary of attitudes and perceived barriers to partner notification for STIs
4. Uptake, yield and prevalence of STI in intervention clusters that offer STI testing.
5. Quantitative analysis of the association between acceptance of STI testing and predictive factors
6. Prevalence of STIs by study arm

### ***p. 5.6 Pilot study of investigation into prevalence of exposure to trauma***

#### **i. 5.6.1 Background and description**

Trauma exposure in youth as described in the Diagnostic and Statistical Manual 5 involves danger of death, injury, physician or sexual abuse, war, conflict and chronic disease that can predispose young people to diverse mental health problems specifically post-traumatic stress disorder (PTSD). Research, mostly from high-income settings, has shown that post-traumatic stress disorder (PTSD), depression and substance use are common in young people who experience trauma. The consequences of the mental disorders can be far reaching, including reduced quality of life, increased use of mental health services and impaired functioning. There is also increasing evidence of a link between repeated traumatic exposures and effects on physical health. People living in LMICs like Zimbabwe likely have more exposure to “trauma” than those living in high-income settings including higher levels of interpersonal violence and socioeconomic stressors. In addition, the recent COVID19 pandemic and the consequent control measures such as restricted movement and lockdowns may be experienced as a traumatic life-event. The CHIEDZA project provides an opportunity to conduct a pilot to investigate if young people do report high levels of trauma. This pilot will inform a more in-depth investigation of the prevalence

of trauma, the types of trauma, its consequences and the appropriate interventions that should be developed and implemented.

A convenience sample of 100 individuals aged 18-24 years accessing the CHIEDZA intervention (in Harare province only) who provide written informed consent will be recruited to determine the traumatic events that young people go through using the Life events checklist (LEC). The measure is designed to screen for potentially traumatic events in a respondent's lifetime. It assesses exposure to 16 events that are associated with development of PTSD. The scale includes one additional item assessing any other extraordinarily stressful event not captured in the first 16 items. This will be complemented by qualitative interviews in approximately 30 participants who have experienced traumatic events to learn about the traumas experienced and their mental health consequences and their health seeking behaviour. The LEC and interviews will be administered by a trained clinical psychologist and anyone identified with PTSD will be referred for clinical care to Parirenyatwa Hospital, with management costs to be covered by the study.

- **6. Data management**

There are different forms and uses of data within the study.

**q. 6.1 Process data for intervention delivery**

**i. 6.1.1 Identification of service users**

To make the intervention ‘youth friendly’, identifying information such as name and address will not be recorded for clients accessing the CHIEDZA intervention. Instead, biometrics (fingerprint recognition) will be used to record visits and the services received. At the first visit to the CHIEDZA service, demographic data (age, sex, date of birth and initials) will be recorded and fingerprints collected. Clients will choose a memorable password which will be used to identify the correct match at subsequent visits. If biometric identification is not possible or clients decline to provide fingerprints, this will not be a reason to deny services. A backup registration process will be available, consisting of an ID number allocated to the client.

**ii. 6.1.2 Monitoring service use**

Individuals accessing the CHIEDZA service will be identified only by their fingerprints on each visit, except for certain services (see below). Fingerprint recognition operates by returning the most closely matching 3-5 records in its database. In the event that the password is forgotten, age, sex and initials will be used to verify the match. At each visit the client makes, the services accessed will be recorded (Figure 5). Where serious concerns are identified (red-flag), personal details will be collected to follow-up on concerns. The only information from previous visits available to a member of CHIEDZA service staff through the fingerprint match will consist of:

- HIV status
- Date of last HIV test
- Red flag

. For those who test HIV-positive, identifying data including name and address and contact/locator details will be collected. This will be done to register them into the national HIV programme and to follow-up those who do not attend for drug collection. Attendance at CAPS groups, and ART prescribed and dispensed will be recorded and transcribed into the national ART programme records.

Demographic data at registration and services accessed at visits will be recorded off-line using an Android based data capture application called Survey CTO Collect. SIMPRINTS biometric technology will be integrated with Survey CTO to track visits to the CHIEDZA and services accessed at each attendance. After the data are collected off-line, it will be synchronised over our local wi-fi network to the Survey CTO Server. Data will be quality controlled on a real-time basis using automated quality checks.

Access to the data will be limited to the Data Management personnel and specified study personnel. The data collection and entry processes will be as detailed in Standard Operating Procedures. Data will be quality controlled on a real-time basis using automated quality checks.

## ***r. 6.2 Outcome data from cross-sectional survey***

The cross-sectional survey will be conducted at community level by trained research assistants, using electronic tablets with pre-designed data entry forms including validation checks and skip patterns. Fingerprints will be collected from each survey participant. The research assistants will ask questions and fill in answers on the tablet. For sensitive questions, the participant will input the answers directly to prevent social desirability bias. Biometric records obtained from participants in the cross-sectional survey will be matched against all biometric records of clients accessing the intervention to assess degree of contamination and coverage of the intervention.

**Figure 6: Different forms of data and linkage to fingerprints**

[figure not shown]

## • **7. Statistical considerations and Data analysis**

### **s. 7.1 Outcomes**

All outcomes will be measured in the cross-sectional survey after 2 years of implementation.

The primary endpoint is the proportion of HIV positive participants in the survey who have virological suppression (viral load <1000 copies/ml), by arm.

The secondary outcomes are

- Proportion of HIV positive participants who are aware of their HIV status
- Proportion of those aware of their HIV positive status who are taking ART
- Proportion of those on ART who are virally suppressed

These outcomes correspond to the individual UNAIDS 90-90-90 targets, while the primary endpoint is the product of all three.

Other outcomes will be measured among all survey participants, regardless of HIV status. They are

- Proportion with knowledge of their HIV status
- Proportion with STIs
- Proportion of males circumcised
- Proportion of females using modern methods of contraception
- Proportion with good MHM (defined as using a clean menstrual management material to absorb or collect blood that can be changed in privacy as often as necessary for the duration of the menstruation period, using soap and water for washing the body as required, and having access to facilities to dispose of used menstrual management materials)
- Proportion with symptoms of common mental disorders (measured using the Shona Symptom Questionnaire-14 with a cutpoint of 9)
- Proportions who report tobacco, alcohol and substance use
- Sexual behavior (including no. of sexual partners in the past year and condom use)

ART drug resistance will be measured in samples that are virologically non-suppressed (subject to funding).

### **t. 7.2 Sample size calculations**

For the primary outcome, we assume that

- the community prevalence of HIV in the population aged 18-24 (the age range of the cross-sectional survey) is conservatively estimated at 3.0%-based on a prevalence of 3.6% in 15-19 year olds and 5.5% in 20-24 year olds in the ZIMPHIA survey (a national population-based survey conducted in Zimbabwe between 2015-2016)
- the coefficient of variation in HIV prevalence between clusters is 0.25-0.3

- The primary outcome is the proportion of young people living with HIV who are virally suppressed, expected to be 43% in the control arm (60% diagnosed x 70% linked to care x 63% virally suppressed).

The trial is aiming to meet 90-90-90 targets and has >90% power to detect a difference (73% in the intervention arm). However, this is an aspirational target and the study will have enough power to detect a smaller difference in the primary outcome. The study continues to have high power in the scenarios of lower HIV prevalence or increased variation in HIV prevalence between clusters. The study has not been powered to undertake stratified analysis by sex or assess any differences in impact between them.

Using the *clustersampsi* command in Stata gives the following projections:

**Table 6: Sample size calculation for primary outcome**

| Cluster size | HIV prevalence | Number HIV+ per cluster | Expected outcome in control arm | Power | Coefficient of variation | Minimum outcome prevalence in intervention arm that will show effect |
|--------------|----------------|-------------------------|---------------------------------|-------|--------------------------|----------------------------------------------------------------------|
| 1000         | 3%             | 30                      | 43%                             | 80%   | 0.25                     | 62%                                                                  |
| 1000         | 3%             | 30                      | 43%                             | 80%   | 0.3                      | 66%                                                                  |
| 1000         | 3%             | 30                      | 43%                             | 90%   | 0.25                     | 66%                                                                  |
| 1000         | 3%             | 30                      | 43%                             | 90%   | 0.3                      | 70%                                                                  |
| 700          | 3%             | 21                      | 43%                             | 80%   | 0.25                     | 64%                                                                  |
| 700          | 3%             | 21                      | 43%                             | 80%   | 0.3                      | 67%                                                                  |
| 700          | 3%             | 21                      | 43%                             | 90%   | 0.25                     | 67%                                                                  |
| 700          | 3%             | 21                      | 43%                             | 90%   | 0.3                      | 71%                                                                  |

The secondary outcomes rely on self-report of HIV-positive status and 2) ART use. In the ZIMPHIA survey, 50% of 15-24 year olds reported being HIV-positive, 83.7% of these reported using ART and of these 85.4% were virally suppressed. The first step of the HIV care cascade (HIV testing) appears to be the main step that will drive the difference in the primary outcome and the trial is powered to detect a difference in this step, including if there are higher proportions of those who report being HIV positive and a smaller difference between the control and intervention arms. The trial will not be powered to detect a difference in the second and third steps of the HIV care cascade.

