Participants will be asked about knowledge of HIV status, history of HIV testing (including date of, place of and reason for test) and whether accessing HIV care/on ART, where they are accessing ART and ART adherence. Participants will be asked about their sexual behaviour (including VMMC (males only); pregnancy history, use of contraception and MHM (females only); and condoms (all)), and other risk behaviours such as smoking, alcohol and substance use and common mental disorders using validated tools. Blood pressure, height and weight will be measured. Participants will be provided with information about risk behaviours and those who meet pre-defined criteria for common mental disorder or harmful substance use or severe hypertension will be referred for appropriate care. All participants who do not want to disclose their HIV-status or do not have documented evidence of an HIV-positive test and want to know their HIV status will be referred to the local health facility for HIV testing and counselling. A blood sample for anonymised HIV antibody testing and an HIV VL (and drug resistance testing- will be collected. HIV VL will only be done on samples that test HIV-positive in the laboratory.

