##### **i. 8.4.1 Benefits and risks at community level**

If the intervention is effective, this will lead to increased level of viral suppression at population level and contribute to meeting the ambitious UNAIDS 90-90-90 targets to help end the HIV epidemic. This age-group has disproportionately poor outcomes compared to other age groups (e.g. 45% viral suppression in 15-24 year olds compared to 60% in older age groups). The intervention will likely have an impact on HIV incidence (although the study is not powered to detect this) as well as improved SRH. If the trial shows that the intervention is highly effective and cost-effective, efforts will be made to ensure that the control communities are among the first to benefit from this intervention.

Any community-based research project may present risks to a community. Communities may feel disempowered by having a research agenda imposed on them or they may be placed at risk of stigmatization by the publication or dissemination of research results. Large community research projects may disrupt intra-community social structures and networks that may not have been identified by the research team. We will conduct a detailed process evaluation, which will measure such harms and also have systems for monitoring and addressing social harms (see below). Communities will not be named in any publication or dissemination of results of the study. There could be an additional burden placed on already overwhelmed routine services. The intervention includes provision of ART and other services at community level and this may mitigate against this risk. The study team will work closely with government agencies and will not entice staff away from them by offering differential salary packages. Communication will be maintained with study communities for the duration of the study and a well-developed exit strategy will be planned with the input of all stakeholders and community engagement structures to ensure that there is a seamless transition from study to routine health services at the end of the study.

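### Awareness and ART use are self-reported while the primary is laboratory-measured, so the cascade steps need not multiply to the primary; and steps 2 and 3 are compared by arm in groups the intervention is meant to change

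*Combined protocol and SAP*

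**What the plan says.** Section 7.1 defines the primary endpoint by laboratory viral load among all HIV-positive participants, whatever they report. It then lists three secondary outcomes:

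- Step 1: "Proportion of HIV positive participants who are aware of their HIV status"
- Step 2: "Proportion of those aware of their HIV positive status who are taking ART"
- Step 3: "Proportion of those on ART who are virally suppressed"

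It adds: "These outcomes correspond to the individual UNAIDS 90-90-90 targets, while the primary endpoint is the product of all three".

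Section 7.2, between Tables 6 and 7, gives the basis of measurement: "The secondary outcomes rely on self-report of HIV-positive status and 2) ART use". It also says the trial is not powered for steps 2 and 3, and names HIV testing as the main driver of any difference in the primary.

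Section 7.3 applies one analysis to every outcome: cluster risks, then a regression of log risk on stratum and arm to give a risk ratio with a 95% CI. It has no rule for misreported status or ART use, and no version of step 2 over all HIV-positive participants.

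Section 5.1 foresees non-disclosure, in a referral rule that begins: "All participants who do not want to disclose their HIV-status or do not have documented evidence". Section 6.2 has participants enter sensitive answers themselves. Section 9.1 runs viral load on every HIV-positive sample.

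**The concern.** There are two separate problems.

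**Measurement.** A participant who is on ART and suppressed, but does not report a positive status, counts as suppressed in the primary and as unaware in step 1, and is absent from steps 2 and 3. Someone who reports the status but not the ART is lost from step 2 onwards. The two measurement systems then cannot be expected to satisfy the identity in section 7.1. Non-disclosure is plausible here: the interview is at the household, and section 9.1 rules out home HIV testing because youth fear unintended disclosure and lack of privacy. Only the intervention arm has peer groups, supportive SMS and a youth-friendly HIV service (sections 3.2.3 and 3.3.1), so willingness to disclose could differ by arm.

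**Denominators.** Steps 2 and 3 are taken among those aware and those on ART. The intervention is designed to enlarge both groups, and Table 7 plans for awareness of 80 to 90% against 60%. A risk ratio within those groups compares people selected after randomisation.

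At stake is the explanation of why the primary moved or did not. The primary itself is not at risk.

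**Working it through.** **1. The identity, on the protocol's own figures.** Section 7.2 cites the national survey for ages 15-24: 50% reported being positive, 83.7% of these reported ART, and 85.4% of these were suppressed. Section 8.4.1 cites the same survey for "45% viral suppression in 15-24 year olds".

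- Reported cascade: 0.50 × 0.837 × 0.854 = 35.7%
- Gap: 45.0 − 35.7 = 9.3 points; 9.3/45 = 21% of the suppressed

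This is a ceiling on suppressed non-disclosers. It assumes that both figures share a denominator and definition of suppression, and that nobody is suppressed off ART.

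**2. Table 7 reproduced.** With c = 12 clusters per arm, m = 21 HIV-positive per cluster and two-sided 5% (assumed; section 7.2 gives no alpha, section 7.3 uses 95% CIs):

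power = Φ( |p1 − p0| × √[(c − 1)/V] − 1.96 ), where V = p0(1 − p0)/m + p1(1 − p1)/m + k²(p0² + p1²)

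| Rates | k | Table 7 | Formula |
|---|---|---|---|
| 60 vs 90% | 0.25 | 92% | 91.6% |
| 60 vs 90% | 0.3 | 82% | 81.6% |
| 60 vs 80% | 0.25 | 64% | 64.2% |
| 60 vs 80% | 0.3 | 52% | 51.9% |

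**3. Equal non-disclosure.** Assume 20% of aware youth in each arm do not disclose, nobody falsely reports awareness, and Table 7's rates are true awareness. Then 60 vs 80% is observed as 48 vs 64%.

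- Risk ratio: 80/60 = 1.33 and 64/48 = 1.33, unchanged
- k = 0.25: V = 0.0229 + 0.0400 = 0.0629; 0.16 × √(11/0.0629) − 1.96 = 0.16; power 56% (from 64%)
- k = 0.3: V = 0.0229 + 0.0576 = 0.0805; 0.16 × √(11/0.0805) − 1.96 = −0.09; power 46% (from 52%)

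**4. Disclosure that differs by arm.** With equal true awareness, the observed risk ratio is the ratio of the disclosure rates. The documents give no rates by arm, so these are assumptions:

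- 84% control vs 90 to 95% intervention: 1.07 to 1.13
- 84% control vs 80% intervention: 0.95

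The 84% is what step 1 implies if the whole gap lies among those not reporting a positive status: 50/(50 + 9.3).

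**5. Conditional denominators.** Assumed example: 60% aware, of whom 83.7% are on ART; the intervention adds 20 points of newly aware youth, 60% of them on ART.

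- Step 2: 83.7% becomes (60 × 0.837 + 20 × 0.60)/80 = 77.8%
- ART among all HIV-positive: 60 × 0.837 = 50% becomes 50.2 + 12 = 62%

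With 70% of the already aware on ART (section 7.2's planning value for linkage to care) and 40 to 60% of the newly aware starting, the step 2 risk ratio is 0.89 to 0.96, while ART among all HIV-positive rises from 42% to 50-54%, a risk ratio of 1.19 to 1.29. The two measures point in opposite directions.

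**6. Reclassifying by viral load.** Counting everyone suppressed as aware and on ART, with the whole gap among non-reporters, the survey cascade becomes 59.3% × 86.2% × 88.0% = 45.0%. The identity is restored, but by construction, and step 3 rises from 85.4% to 88.0% because unsuppressed non-disclosers stay out. The rule can also create an arm difference. Assume true awareness of 60% and non-disclosure of 20% in both arms, with suppression among the aware of 60% vs 80%, unrelated to disclosure:

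- Self-report: 48% vs 48%, risk ratio 1.00
- Reclassified: 0.6 × (0.8 + 0.2 × 0.6) = 55.2% vs 0.6 × (0.8 + 0.2 × 0.8) = 57.6%, risk ratio 1.04

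**The case against.** The other side has several good points, and they limit the claim.

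- A reader might infer that non-disclosure shrinks the awareness effect. On the planned scale it does not: equal non-disclosure cancels from the risk ratio. Only the risk difference and the precision suffer.
- A reader might take the 9.3 points as measured non-disclosure. The protocol gives no denominator or threshold for the 45%, and some people may be suppressed without ART. It is a ceiling under stated assumptions.
- The power loss may be counted twice. Section 7.2 introduces Table 7 partly in terms of who reports being positive, so its rates may already be self-reported; elsewhere it calls the 60% diagnosed. The text is ambiguous.
- A reader might extend the denominator problem to all three steps. Step 1 already uses all HIV-positive participants, and suppression over all HIV-positive is the primary. Only ART use lacks such a version.
- The conditional steps are deliberate. Sections 2.2 and 7.1 tie them to 90-90-90, and as description they are sound. The caveat in section 7.2, however, is about power and does not cover selection.
- Self-entry of sensitive answers should reduce misreporting. It cannot be assumed to remove it.
- It is tempting to make viral-load reclassification the main definition. Step 6 shows why not: it corrects more fully in the arm with better suppression.

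None of this rescues the product statement or makes steps 2 and 3 randomised comparisons.

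**Conclusion.** The point holds as a cheap improvement. As measured, the primary is the product of the three steps only if status and ART use are fully reported and suppression occurs only on ART. The possible shortfall is up to 9.3 points on the survey figures, under the assumptions in step 1. If Table 7's rates are true awareness, 20% non-disclosure in both arms costs 6 to 8 points of power for 60 vs 80%, with no change in the risk ratio.

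Bias in step 1 from disclosure that differs by arm is possible but not shown, and its direction is unknown. The documents do not support a claim that the intervention would look falsely better, or falsely worse, on awareness.

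For steps 2 and 3 the problem is structural and does not depend on misreporting, although the sizes above come from assumed inputs.

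**What to change.** In sections 7.1 and 7.3:

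- **ART use.** Make the between-arm comparison over all HIV-positive participants, beside awareness over all HIV-positive (already step 1) and the primary. Present conditional steps 2 and 3 by arm as description, without an effect claim.
- **Self-report.** Keep it as the main definition. Add a pre-specified sensitivity analysis that classes every HIV-positive participant with viral load below 1000 copies/ml as aware and on ART, in both arms. State its limits: it corrects only suppressed non-disclosers, so correction is fuller in the arm with better suppression; it inflates step 3; and it misclasses people who control the virus without ART.
- **Wording.** Qualify "while the primary endpoint is the product of all three" to say that this holds only when status and ART use are fully reported and suppression occurs only on ART.

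Do not rely on CHIEDZA service records alone to correct self-report, since they would mainly correct the intervention arm.

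The cost is wording, a little more analysis, and one extra set of figures beside the 90-90-90 display. No new data are needed.
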